#### Measurements of postural sway

Static postural sway will be assessed using a force platform (Fusyo™) under four conditions, in the following order:

1. Bipedal stance with eyes open;

2. Bipedal stance with eyes closed;

3. Monopedal stance on nonaffected leg, with eyes open; and

4. Monopedal stance on affected leg, with eyes open.

The first condition will be performed twice: the first time to acclimatize the subject and the second time for the measurement. The data will be acquired at 40 Hz over a period of 52 seconds, in accordance to the ‘Normes 85’ of the French Association of Posture and Equilibrium [17].

During all balance tests, subjects will be told to look straight ahead. During the bipedal stance, subjects will stand barefooted on the force platform with their feet positioned at shoulder width and their arms by their sides. For each subject, the positions of the footplates will be adjusted to match the subject’s normal stance. During the monopedal, stance subjects will be instructed to hold their contralateral limb at 90° of knee flexion for the duration of the test. Before starting the test and data collection, the subjects will be allowed to settle into a good test position. When the subjects will be ready they will be asked to say ‘ready’ and data collection will start. The subjects will be allowed to practice each test condition a few times before the actual measurements will be taken.

#### Spatiotemporal parameters

A 7.93-meter-long computerized treadmill (Gaitrite™, CIR Systems Inc.) will be used. Patients will be instructed to walk barefoot at a self-selected speed as previous studies have shown that this gives a consistent result for the gait parameter [18]. Each evaluation will include four comings and goings. The mean value of the eight tests will be analyzed for each parameter.

The following spatiotemporal parameters will be evaluated: absolute velocity (m/s), normalized velocity (m/s/leg length), cadence (steps/min), step length (m), normalized step length (m/leg length), swing phase (% gait cycle), stance phase (% gait cycle), single limb support phase (% of gait cycle), double limb support phase (% gait cycle), and base of support (m).

### Statistical considerations

#### Justification of the number of subjects to be included

The principal objective of this study lies in the assessment of the increase in the quadriceps isokinetic peak torque of the treated knee as measured using a Cybex Norm™ computerized dynamometer, with the concentric mode, at a speed of 60/second after treatment.

The estimation of sample size was determined on the basis of a greater improvement of muscular strength in the quadriceps of the treated knee (muscular strengthening in the medical treatment of the femorotibial knee osteoarthritis) in the eccentric group compared to the concentric group. From the work of Tüzun *et al.*[10] and Huang *et al*. [9], we learned about the increase in muscular strength of the quadriceps using isokinetic concentric training. The difference between the two groups was estimated at 15% (treated as quantitative) and the standard deviation was fixed at 20 (supposedly identical in the two groups). Also, for a type I error α and a statistical power fixed respectively at 5% (in a two-sided situation) and 90%, 40 patients per group need to be recruited. The rate of ‘lost to view’ for the measurement of the principal endpoint criterion at 6 weeks is considered negligible [10].

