#### Randomization

Included patients will be randomly allocated to either arm (training group) in a 1:1 ratio. The randomization list will be generated by block randomization. Randomization will be performed automatically (using software) by an independent statistician once a patient will be considered eligible and informed consent will be obtained.

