#### Principal analysis

The principal endpoint criterion is the improvement at 6 weeks of treatment of the isokinetic concentric quadriceps peak torque at the speed of 60°/s. The comparison between the randomized groups will be performed using the Student test or the Mann and Whitney test (if the conditions for validity of the Student test are not respected). The comparison between the treatment groups will be performed systematically: 1) without adjustment and, 2) by adjusting other factors whose repartition could be, despite the randomization, unbalanced between the treatment groups.

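### The sample size assumes a relative gain in peak torque, but the primary analysis does not say whether improvement is percent or absolute and does not commit to adjusting for baseline torque

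*Protocol article*

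**What the plan says.** Under *Justification of the number of subjects to be included*, the protocol article sets type I error and power, "fixed respectively at 5% (in a two-sided situation) and 90" per cent respectively. It then gives the effect assumption: "The difference between the two groups was estimated at 15% (treated as quantitative) and the standard deviation was fixed at 20". The difference carries a percent sign; the standard deviation carries no unit. The conclusion is that "40 patients per group need to be recruited", and loss to follow-up "for the measurement of the principal endpoint criterion at 6 weeks is considered negligible". *Randomization* states that patients are "randomly allocated to either arm (training group) in a 1:1 ratio".

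Under *Principal analysis*, the endpoint is "the improvement at 6 weeks of treatment of the isokinetic concentric quadriceps peak torque at the speed of 60°/s". The groups are compared by a Student test, or by Mann–Whitney if the Student conditions fail. The comparison is made once without adjustment and once adjusted for factors whose distribution turns out unbalanced. Baseline peak torque is not named as a covariate. Neither section says whether improvement is a percent change from baseline or a difference in torque units.

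**The concern.** A relative gain and a torque gain are different variables with different standardised differences. A power figure calculated for one does not carry over to the other without knowing how baseline torque varies and how gain relates to it. The article attaches its 90% to a relative scale and then names an endpoint that fits either scale.

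Two things are at stake. First, the power claim cannot be checked on the scale that will be tested, and the margin is thin. With 40 per group, 90% power needs a standardised difference of 0.734, and the plan assumes 15/20 = 0.75. Second, the wording leaves several routes to the primary result: percent or absolute change, Student or Mann–Whitney, and unadjusted or adjusted for covariates chosen after looking at imbalance. Baseline torque is measured on every patient and is the obvious covariate, yet it enters only if it happens to be unbalanced.

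**Working it through.** **1. Reproduce the plan's figure.** Inputs from the sample-size section: difference 15, SD 20, two-sided 5%, power 90%, no loss; allocation 1:1.

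- Normal approximation: n = 2 × (1.960 + 1.282)² × (20/15)² = 37.4, so 38 per group.
- Two-sample t: 38.35, so 39 per group.
- t-test figure divided by 0.955 (Mann–Whitney efficiency under normality): 38.35/0.955 = 40.2.
- Power at 40 per group: 91.8% (normal) or 91.2% (t).

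The stated 40 is reproduced when 15 and 20 are both percentage points of gain.

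**2. Percent gain as planned, analysed as raw change.** Suppose percent gain has SD s = 20 and is independent of baseline. Raw gain is baseline × percent gain. In units of 1% of mean baseline, its variance in an arm with mean gain m is (1 + CV²)(s² + m²) − m², where CV is the baseline coefficient of variation. CV and m are assumptions, because the article gives neither.

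Example with CV 0.30 and gains of 20% and 35%:
- Concentric: 1.09 × (400 + 400) − 400 = 472.
- Eccentric: 1.09 × (400 + 1225) − 1225 = 546.25.
- Pooled SD = √509.1 = 22.56; standardised difference 15/22.56 = 0.665; power about 84%.

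Over assumed concentric gains of 10–40% and CV 0.2–0.5, power by this formula runs from 89% down to 52%. With CV 0 it stays at 91%.

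**3. The reverse model.** Suppose instead that raw gain is independent of baseline, with arm means of 20% and 35% of mean baseline and SD 20% of mean baseline. Percent change is now the noisier variable. Simulated power for both models (40 per arm, lognormal baseline, two-sided 5%, 20,000 runs, centre not modelled):

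| Analysis | Gain arises as percent: CV 25/35/40/50% | Gain arises as raw torque: CV 25/35/40/50% |
|---|---|---|
| t-test, percent change | about 91% throughout | 86/81/79/73% |
| t-test, raw change | 86/81/79/73% | 91–92% throughout |
| ANCOVA, raw torque on baseline | 89/88/87/84% | about 91% throughout |
| ANCOVA, log torque on log baseline | 90–91% throughout | 89/88/87/85% |

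The two unadjusted tests swap places between the models. Taking separate runs of this comparison together, unadjusted power on the mismatched scale is about 71–88%, and log ANCOVA gives about 85–94% under both models.

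**4. SD 20 read as Nm.** If the difference is 15% of an assumed mean baseline and the SD is 20 Nm, a mean baseline of 60 Nm gives 9/20 = 0.45 and 51% power. At 80 Nm power is 76%, at 100 Nm 91%, and at 150 Nm above 99%. The missing unit alone leaves the claim uncheckable on this reading.

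**5. Points of gain are not a ratio.** Gains of 35% and 20% give 1.35/1.20 = 1.125. With 25% and 10% the ratio is 1.25/1.10 = 1.136; with 55% and 40% it is 1.55/1.40 = 1.107. None is 1.15.

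**The case against.** The most natural joint reading is percent improvement. The sample size speaks of improvement and a 15% difference, and the endpoint uses the same word. On that reading the arithmetic reproduces and nothing is contradicted. The article also condenses a fuller protocol, and the exact derivation of a change variable is commonly left to that document or to the SAP. This stands to the extent that the unstated scale alone would be missing detail rather than an error.

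A reader might go further and infer that the trial misses its 90% power because raw torque gains are noisier than percent gains. The document does not support that. It never commits to raw units, and it gives no baseline torque, no baseline spread and no SD of raw change. The raw-scale loss in step 2 follows from assuming percent gain independent of baseline; under the reverse assumption the loss falls on percent change instead.

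The article also promises an adjusted comparison, and adjustment recovers part of any loss. But its covariates are those found unbalanced, so baseline torque is not assured, and it is not said which comparison is primary.

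Finally, log ANCOVA is not uniformly best. Where an unadjusted test matches the way gains arise, that test does as well or slightly better. The log scale is a reasonable choice, not the only one.

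**Conclusion.** The point holds as a matter of definition and of analysis choice, not as an arithmetic error. The stated 40 per group and 90% power are right for percentage points of relative gain. The principal analysis does not tie its test to that scale, and it leaves out a committed adjustment for baseline torque that would make the result less dependent on the scale.

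Under assumed baseline CVs of 25–50% and gains of 20% and 35%, an unadjusted test on the wrong scale costs roughly 3 to 20 points of power (about 91% falling to 71–88%), whether the wrong scale is raw or percent. Baseline-adjusted analysis limits this: log ANCOVA stays at about 85% or above under both models. These sizes rest on assumed baseline spread, an assumed concentric gain and two simple models of gain. They show how sensitive power is to the scale; they do not predict this trial's power. It would be worth settling before analysis, but it does not call for a larger sample.

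**What to change.** - In *Justification of the number of subjects to be included*, state that 15 and 20 are both percentage points of gain relative to baseline.
- In *Principal analysis*, name one primary analysis in advance: ANCOVA of week-6 concentric peak torque at 60°/s on baseline peak torque, with centre as a covariate. The log scale is preferable because it keeps a relative effect; report the back-transformed ratio of geometric means with its confidence interval.
- Keep the unadjusted comparisons of percent change and raw change as supportive results.
- State the target on the scale chosen. A 15-point difference in gain should not be written as a ratio of 1.15; with gains of 35% and 20% it is 1.125, and it shifts with the assumed concentric gain.

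The cost is a few sentences of wording, with no new data and no extra patients. The small downside is that the main result is read as a ratio rather than in torque units, which the supportive raw change offsets.

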#### Principal analysis

The principal endpoint criterion is the improvement at 6 weeks of treatment of the isokinetic concentric quadriceps peak torque at the speed of 60°/s. The comparison between the randomized groups will be performed using the Student test or the Mann and Whitney test (if the conditions for validity of the Student test are not respected). The comparison between the treatment groups will be performed systematically: 1) without adjustment and, 2) by adjusting other factors whose repartition could be, despite the randomization, unbalanced between the treatment groups.

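### A check on the outcome data chooses between Student and Mann-Whitney for the primary test; if gains are skewed and spreads also differ, this rule can reject equal mean gains well above 5%

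*Protocol article*

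**What the plan says.** Under Principal analysis, the primary endpoint is the "improvement at 6 weeks of treatment of the isokinetic concentric quadriceps peak torque at the speed of 60°/s". The arms are compared "using the Student test or the Mann and Whitney test (if the conditions for validity of the Student test are not respected". The section names no check, threshold or variable for that decision. It then asks for the comparison both without adjustment and with adjustment for factors that turn out unbalanced.

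The sample-size section is written in terms of means. It states "The difference between the two groups was estimated at 15% (treated as quantitative". Its assumption about spread is that "the standard deviation was fixed at 20 (supposedly identical in the two groups". Type I error and power are "fixed respectively at 5% (in a two-sided situation) and 90" percent, from which "40 patients per group need to be recruited". Loss to follow-up "for the measurement of the principal endpoint criterion at 6 weeks is considered negligible". Under Randomization, patients are "randomly allocated to either arm (training group) in a 1:1 ratio".

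**The concern.** The two candidate tests target different quantities. Student's test compares mean gains, which is what the trial was sized on. Mann-Whitney asks whether a gain drawn from one arm tends to exceed a gain drawn from the other. The two agree when the arms differ only by a shift, but can disagree when the arms differ in spread and the gains are skewed.

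The mechanism is easy to see with exponential-shaped gains, whose median lies below the mean by (1 − ln 2) = 0.307 SD. With equal means and SDs of 20 and 40, the medians lie 0.307 × 20 = 6.1 and 0.307 × 40 = 12.3 below that common mean. They differ by about 6 although the mean gains are identical. Ranks respond to that gap. A significant primary result could then reflect unequal variability rather than a greater mean gain. With right-skewed gains it would tend to favour the less variable arm, whichever that is.

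Skewed gains are also the case in which a normality check sends the analysis to Mann-Whitney. The safeguard would therefore replace a test that holds its level with one that does not, for equality of means. Skewed gains and unequal spreads are not far-fetched: the sizing difference is a percentage, percentage changes can be right-skewed, and two training modes may produce different spreads.

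**Working it through.** **1. The plan's own figure.** Inputs from the sample-size section: difference 15, common SD 20, two-sided alpha 5%, power 90%, no loss; 1:1 allocation from Randomization.

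n per group = 2 × (1.960 + 1.282)² × 20² / 15² = 2 × 10.51 × 1.778 = 37.4, so 38. The t-based calculation gives 38.3, so 39. At 40 per group, power is 91.8% (normal) or 91.2% (t). The stated 40 is reproduced, and it is a calculation for a difference in means.

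**2. What had to be assumed.** The article gives no switching criterion, skewness or arm-specific SDs. Assumed: a switch to Mann-Whitney if Shapiro-Wilk p < 0.05 in either arm or Levene p < 0.05. Gains were simulated with equal means, 40 per arm, SD 20 in one arm and 20 × ratio in the other.

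**3. Rejection rate of the switching rule, nominal 5%** (3,000 runs per cell):

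| Shape of gains | ratio 1 | 1.25 | 1.5 | 2 | 3 |
|---|---|---|---|---|---|
| Normal | 5.8% | 4.9% | 4.6% | 5.8% | 6.6% |
| t, 4 df | 5.4% | 4.6% | 5.2% | 5.1% | 6.6% |
| Lognormal, sigma 0.5 | 4.6% | 6.7% | 10.4% | 16.2% | 25.6% |
| Gamma(2) | 4.8% | 7.2% | 10.6% | 16.0% | 24.9% |
| Exponential | 5.0% | 10.4% | 18.0% | 32.3% | 43.9% |
| Lognormal, sigma 0.8 | 5.0% | 10.8% | 19.9% | 37.2% | 54.3% |

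Monte Carlo standard error: √(0.05 × 0.95 / 3,000) = 0.4 points near 5%, and √(0.17 × 0.83 / 3,000) = 0.7 points near 17%. Separate simulations of the gamma(2) case gave 6.6-7.4%, 10.3-11.4% and 16.6-17.0% at ratios 1.25, 1.5 and 2, in agreement with the table. For milder skew, gamma(8) with skewness about 0.7, the rule gave 5.1%, 6.3% and 7.8% at those ratios (4,000 runs). In the four skewed rows, Shapiro-Wilk alone triggered the switch in 97-100% of trials.

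**4. Welch's test on the same scenarios** (10,000 runs per cell):

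| Shape of gains | ratio 1 | 1.25 | 1.5 | 2 | 3 |
|---|---|---|---|---|---|
| Normal | 5.4% | 5.2% | 5.1% | 4.8% | 4.9% |
| t, 4 df | 4.9% | 4.5% | 4.8% | 5.1% | 4.7% |
| Lognormal, sigma 0.5 | 4.7% | 4.8% | 5.2% | 5.1% | 5.4% |
| Gamma(2) | 4.6% | 5.0% | 5.0% | 4.9% | 5.8% |
| Exponential | 5.0% | 4.7% | 4.9% | 5.6% | 6.2% |
| Lognormal, sigma 0.8 | 4.3% | 4.4% | 5.5% | 6.5% | 7.4% |

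Because the arms are equal in size, Student's test is almost the same; its worst cell is 7.5% (lognormal sigma 0.8, ratio 3). For gamma(8), both tests stay at 4.8-5.2%.

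**5. Power.** Using Mann-Whitney on normal data (relative efficiency 3/π = 0.955) gives 89.9% power at 40 per arm, against 91.2% for the t test. For gamma(2) gains with equal SD 20 and a shift of 15, a simulation gave 96.3% for the plan's rule and 90.3% for Welch.

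**The case against.** The case for leaving the rule alone is substantial.

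- **It is declared in advance.** A reader might infer that the hypothesis is quietly changed after the data are seen. The text does not support that: both the fallback and its condition are written down, and the practice is common. What is true is narrower: which of two targets is tested depends on the outcome data.
- **The criterion may stand elsewhere.** The full protocol or an analysis plan may define it, so its absence from an article is not itself the point. A different criterion could also fire less often than the one assumed here. This stands as a limit on the sizes given. But any criterion would still switch between two targets, only one of which the trial was sized on.
- **Unequal spread alone is not enough.** A reader might infer that differing spreads by themselves push the error far above 5%. They do not: symmetric gains stay within 4.6-5.8% up to ratio 2 and reach 6.6% at ratio 3.
- **The objective does not name the mean.** It speaks of a greater improvement in strength. That is fair; the mean enters only through the sizing inputs. Those are nevertheless the only statement in the article of the difference the trial is built to detect.
- **Mann-Whitney is not without an estimate or an adjusted form.** The Hodges-Lehmann shift is in outcome units, and rank-based or ordinal models can adjust for covariates. Neither can be held against the plan.
- **The rank test can help.** With skewed gains and equal spreads it holds 5% and gains power. This stands, and is the real cost of the fix.

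**Conclusion.** The point holds in limited form, as a moderate and cheaply corrected weakness. The primary test is selected from the outcome data between a test of the quantity used for sizing and a test of something else. Under the plan's equal-SD assumption there is no inflation, at 4.6-5.8% for every shape tried. If gains are skewed and spreads also differ, equal mean gains are rejected in about 6-8% of trials for mild skew at SD ratios 1.5-2. The rate is about 7%, 11% and 17% for gamma(2) at ratios 1.25, 1.5 and 2, and up to about 37% at ratio 2 for the strongest skew tried. A mean comparison stays at about 5-6% on the mild and gamma(2) data; Welch reaches 6.5-7.4% only under strong lognormal skew at ratios 2-3.

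These rates rest on the assumed trigger, shapes and SD ratios. They should not be read as the error rate of this trial, because the article gives no skewness and supposes equal SDs.

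**What to change.** Name one primary comparison of means in advance: a linear model of the 6-week torque gain with training group and baseline torque, using heteroscedasticity-robust standard errors. Use Welch's test for the unadjusted comparison. State that both are used whatever normality or variance checks show. Report Mann-Whitney with the Hodges-Lehmann shift as a labelled sensitivity analysis. Since the Secondary analysis section follows the same approach, the same wording should carry over to the continuous secondary endpoints.

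The cost is a change of wording. The sample size stays at 40 per group, with about 91% power. The downside to disclose is lower power than a rank test if gains are clearly skewed or heavy-tailed with equal spreads: about 90% against 96% in the gamma(2) case.

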### Study design

ISOGO is a prospective randomized double center clinical trial with blinded evaluation of the endpoints. The outline of the study is shown in Figure 1.

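### The primary endpoint is compared both unadjusted and adjusted for possibly unbalanced factors, with neither named as decisive; one model with covariates fixed in advance would be a free improvement

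*Protocol article*

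**What the plan says.** All references are to the protocol article.

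- **Endpoint** (Principal analysis): "The principal endpoint criterion is the improvement at 6 weeks of treatment of the isokinetic concentric quadriceps peak torque", measured at 60°/s.
- **Test** (Principal analysis): the group comparison "will be performed using the Student test or the Mann and Whitney test", the second if the conditions for the first fail.
- **Two comparisons** (Principal analysis): "The comparison between the treatment groups will be performed systematically: 1) without adjustment", and then a second one "by adjusting other factors whose repartition could be, despite the randomization, unbalanced between the treatment groups". No sentence gives either priority, and baseline torque is not named as a covariate.
- **Sample size** (Justification of the number of subjects): an unadjusted difference of 15% treated as quantitative, SD 20 in both groups, two-sided 5%, 90% power, 40 per group.
- **Design** (Study design; Randomization): two centres, 1:1 block randomization, no stratification factor mentioned.
- **Reach** (Secondary analysis): secondary endpoints are to be analysed in a similar way.

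**The concern.** Two analyses of one endpoint are always run, so they can fall on different sides of 5%, and the article has no rule for that case. The second analysis draws its covariates from whatever could be unbalanced despite randomization. Read naturally, that means imbalance observed in the trial's own data. Which factors enter, and how many, is then settled after the data are seen.

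Imbalance is also the wrong criterion. A covariate earns its place by predicting the outcome, and that can be judged beforehand. Baseline concentric torque at 60°/s is the obvious candidate and is already measured, yet under this rule it is adjusted for only when chance makes the arms differ on it.

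At stake are a clear answer to the primary objective, some precision, and to a small degree the type I error.

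**Working it through.** **1. The plan's own figure.** Inputs from the sample size section: Δ = 15, SD = 20, α = 0.05 two-sided, power 0.90.

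n per group = 2·SD²·(1.960 + 1.282)²/Δ² = 2 × 400 × 10.51/225 = 37.4, so 38. With the t distribution it is 38.3, so 39. Dividing 38.3 by 0.955, the Mann-Whitney efficiency for normal data, gives about 40. The stated 40 per group therefore reproduces as an unadjusted comparison. Power at 40 per group is 91.2% (t) or 91.8% (normal approximation).

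**2. How often the rule adjusts for baseline torque.** The article gives no imbalance threshold, so p < 0.05, 0.10 and 0.20 are assumed. Under randomization the imbalance p value is uniform, so any one covariate enters in about 5%, 10% or 20% of trials. With 11 independent candidates (assumed), at least one enters with probability 1 − (1 − threshold)¹¹ = 43%, 69% or 91%. Simulation gave 42-43%, 69% and 91-92%.

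**3. Type I error of the two-comparison rule.** This was simulated under the null with 40 per arm, ordinary least squares, and covariates entering on imbalance. The inputs in both sets are assumptions.

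| Setting | Imbalance-selected test | Either test significant |
|---|---|---|
| 4-8 covariates explaining 30-60% of variance; thresholds 0.10, 0.20; 8,000 runs each | 2.2-4.0% | 5.4-6.8% |
| Baseline torque correlated −0.3 to −0.7 with improvement, plus 0-10 others at 0.2; thresholds 0.05, 0.10, 0.20; 10,000 runs each | 1.8-4.8% | 4.7-6.2% |

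The simulation error is √(0.05 × 0.95/10,000) = 0.2 percentage points (also 0.2 with 8,000 runs). In the second set the two comparisons disagreed on significance in 0.6-5.1% of null trials. A single model with baseline torque always included held its size, at 4.7-5.6%.

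The selected test is conservative for a simple reason. When covariates are balanced and left out, their variance stays in the standard error although they contribute little to the difference between arms. The bound for two independent tests, 1 − 0.95² = 9.75%, does not apply, because these two tests are highly correlated.

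**4. Precision forgone.** The residual SD after adjusting improvement for baseline is 20·√(1 − r²), where r is the baseline-improvement correlation. The article does not give r, so a range is assumed. n for 90% power uses the normal approximation.

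| Absolute r | Residual SD | Power at 40 per group, t (normal) | n per group for 90% |
|---|---|---|---|
| 0 | 20.0 | 91.2% (91.8%) | 38 |
| 0.3 | 19.1 | 93.5% (94.0%) | 34 |
| 0.5 | 17.3 | 96.9% (97.2%) | 29 |

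**The case against.** **The unadjusted test seems to lead.** The only tests named, Student and Mann-Whitney, take no covariates, and the sample size rests on an unadjusted difference. The adjusted comparison comes second and has no named model. This stands as a strong hint, so a reader who infers two competing primary analyses goes further than the text. What is missing is a statement of which analysis decides.

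**The covariate rule may be meant as a list fixed in advance.** The wording is conditional, no balance test is stated, and an exact list is commonly left to the analysis plan. The absence of a list is therefore not the point. But the reference to imbalance despite randomization makes imbalance the criterion, and an analysis plan that followed it would inherit that criterion.

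**Stronger readings that the documents do not support:**

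- *Baseline torque is used only by chance.* It enters every patient's improvement score. Only its use as an adjustment covariate is left to chance.
- *Regression to the mean biases the comparison.* Under randomization it acts equally on both arms in expectation. Chance baseline differences and lost precision remain.
- *The selected test breaches its 5% level.* Its simulated size is below 5%. Only an either-significant claim exceeds 5%, slightly, and the article nowhere says that success would be declared that way.
- *The unadjusted analysis is an error.* It is valid and already has about 91% power. Adjustment makes it more efficient.

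**Conclusion.** The point holds as a modest one. The Principal analysis section sets two comparisons of the primary endpoint without saying which decides, and ties adjustment to imbalance rather than to prognostic value. That leaves discretion over the covariates and over the result to report.

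In numbers, an either-significant claim has a type I error of about 5-7%, the imbalance-selected test has a size of about 2-5%, and power at 40 per group could be about 93-97% instead of about 91%. The error rates rest on assumed thresholds, numbers of covariates and correlations. The power gain rests on an assumed correlation of 0.3-0.5 in absolute value between baseline torque and improvement. None of these inputs is in the article.

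The planned sample size is not undermined. The change is a free improvement.

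**What to change.** 1. Name one primary analysis: a linear model (ANCOVA) of the 6-week improvement in concentric 60°/s quadriceps peak torque of the treated knee. Use the percent scale on which the trial was planned, so that the endpoint does not change. Include arm, baseline torque and centre, fixed in advance whatever balance is observed. Report the adjusted difference, its 95% confidence interval and p value.
2. Delete the selection of covariates by imbalance.
3. Keep the unadjusted Student or Mann-Whitney comparison as a labelled sensitivity analysis.
4. Replace the present non-normality fallback with a prespecified rank-based or robust version of the same model, used if residuals are clearly non-normal.
5. Apply the same principle to the secondary endpoints, since they follow the primary approach.

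The cost is analysis wording and about 2 of the 78 residual degrees of freedom (80 patients minus two group means). Baseline torque and centre are already available, so no new patients, visits or measurements are needed.
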